**Enrollment**								
Eligibility screen	×							
Informed consent	×							
Medical history	×							
MRI scanning	×		×					
Interventions								
MLR-DBS surgery		×						
Stimulation parameters		×						
**Allocation**								
DBS group				×	×	×		
Control group							×	×
**Assessments**								
**Primary outcome measure**								
FMA	×		×	×	×	×	×	×
**Secondary outcome measures**								
BBS	×		×	×	×	×	×	×
POMA	×		×	×	×	×	×	×
BI	×		×	×	×	×	×	×
SF-36	×		×	×	×	×	×	×
HAMD	×		×	×	×	×	×	×
AE		×	×	×	×	×	×	×

### Main outcome

#### Motor function intervention effect

The main evaluation index of this study is the improvement of patients’ motor function before and after deep brain stimulation, which is being evaluated through changes in the Fugl-Meyer Assessment Upper Extremity Scale (FMA-UE) (7). FMA-UE is widely used in clinical motor function assessment and is a quantitative stroke-specific scale used to assess motor function, balance, sensation, and joint function in patients with hemiplegia. Each of the five areas contains different assessment items that are scored on a 3-point scale. This scale has good validity and reliability in the stroke population. The scale covers 50 items, with a total score of 226 points (46). There are 17 sports items, with a total score of 100 points, of which the upper limb motor function score is 66 points, the lower limb motor function score is 34 points. The higher the assessment score, the better the patient’s motor function (47).

### Secondary outcome

#### Balance ability

Stroke patients suffer from balance dysfunction due to impaired control of the brain’s central nervous system and sensory or motor conduction pathways. The Berg Balance Scale (BBS) is mainly used to evaluate the balance and coordination abilities of participants during intervention and follow-up (48, 49). This scale is suitable for patients with strokes of various severity. Through assessment, it can identify whether patients need help with their movements and prompt the patient’s prognosis. It is mainly used in subacute and chronic strokes to predict and evaluate balance after stroke. It has reliability and validity, sensitivity is good, and it is currently the most commonly used international balance scale for stroke patients. The form includes a total of 14 items, each item includes 5 levels (0 to 4 points), with a total score of 56 points. Higher scores indicate better balance ability (49, 50).

Post-stroke Spasticity will be evaluated using the modified Ashworth Scale (MAS), a widely-used assessment method. It measures resistance during passive joint movements, especially suitable for patients with hemiplegia. Muscle spasticity is graded from 0 to 4, with higher grades indicating increased tone. MAS has proven reliable and valuable in clinical settings for assessing upper limb muscle spasticity. Notably, up to 97% of chronic stroke patients with moderate to severe motor impairments experience spasticity (51–53).

#### Fall risk

Falls after stroke are common sequelae of poor motor function recovery, which can cause fear of walking, lead to prolonged hospitalization, increase the risk of disability and death, and seriously affect the independence and quality of life after stroke. Performance-oriented activity assessment (POMA) will be used to assess fall risk during intervention and follow-up. A previous study reported that the POMA is an easy-to-administer task-oriented test with higher test weight than other tests such as the time remaining test, one-leg stance test, and functional accessibility test. Reliability, discriminant validity, and predictive validity (54, 55). The total possible score is 28, the lower the score, the greater the risk of falling (56).

#### Activities of daily living

About 75% of stroke patients suffer from varying degrees of disability, and in severe cases, they even lose the ability to take care of themselves (57). In the process of stroke rehabilitation, the training of self-care ability in daily life is also very important and necessary. Participants’ ability to perform activities of daily living will be assessed by the Barthel Index (BI) during the intervention and follow-up periods (58, 59). BI is a widely used clinical assessment method for daily living ability. It can be used not only to evaluate functional status before and after treatment, but also to predict treatment effects, length of stay, and prognosis. It has the advantages of simple evaluation, strong operability, high reliability, and high sensitivity. Previous studies have shown that BI has high internal and external reliability in assessing the daily living activities of stroke survivors. BI consists of 10 items describing different activities, with a total score of 100 points. The higher the score, the better the patient’s independence and the lower the dependence on others.

#### Quality of life

Patients with improved motor function are often accompanied by improved quality of life. Effective rehabilitation treatment can improve the quality of life after stroke, help patients restore function, improve self-confidence and self-esteem, and reintegrate into social life. This study mainly used a 36-item short-form questionnaire (SF-36) to assess patients’ quality of life. The scale includes 8 aspects and 36 items (60–62). It is easy to use, accepted by patients and meets strict reliability and validity standards. A higher assessment score represents a higher quality of life for the patient.

#### Psychological improvement

Patients with post-stroke hemiplegia may develop post-stroke depression (PSD), which is characterized by persistent depressed mood disorder (mood disorder). The overall incidence rate is as high as 40% to 50%, of which about 15% are severe depression, which may be accompanied by severe suicide or even suicidal behavior. This study used the Hamilton Depression Rating Scale (HAMD) for evaluation (63). This scale is simple to operate, has high reliability and validity, and is widely used in clinical applications. Among them, the HAMD-24 is the most clinically used. Therefore, this study evaluated patients before and after HAMD-24 treatment. A total score of more than 8 points indicates the presence of depressive symptoms in patients, and the higher the score, the more severe the depressive symptoms.

#### Adverse events

During the treatment process, a small number of patients may experience symptoms such as accidental injuries, skin rupture and bleeding, muscle soreness, joint pain, and rashes. Any adverse events (AEs) during recovery should be documented in a specific CRF with time of occurrence, severity, relationship to the duration of the intervention, and prognosis. Investigators should take necessary measures to deal with all AEs to ensure the safety of the subjects and follow up with the subjects until their physical condition returns to normal levels. All adverse events (such as pain and falls) occurring during intervention and follow-up will be recorded on a case record form (CRF) through monitoring and self-reporting, and the relevance of the intervention will be assessed. The incidence of an adverse event was defined as the number of patients in whom it occurred divided by the number of all patients. Calculate the number and frequency of adverse events, related adverse events (adverse reactions), adverse events leading to withdrawal, and serious adverse events, and provide detailed records (64, 65).

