**Methods/design:**

This multicenter, prospective, double-blind, randomized crossover clinical trial aims to assess the safety and effectiveness of Deep Brain Stimulation (DBS) in the mesencephalic locomotor region (MLR) for patients with moderate to severe post-stroke hemiplegia. Sixty-two patients with stable disease after a year of conservative treatment will be enrolled and implanted with deep brain electrodes. Post-surgery, patients will be randomly assigned to either the DBS group or the control group, with 31 patients in each. The DBS group will receive electrical stimulation 1 month later, while the control group will undergo sham stimulation. Stimulation will be discontinued after 3 and 6 months, followed by a 2-week washout period. Subsequently, the control group will receive electrical stimulation, while the DBS group will undergo sham stimulation. Both groups will resume electrical stimulation at the 9th and 12th-month follow-ups. Post-12-month follow-up, motor-related scores will be collected for analysis, with the Fugl-Meyer Assessment Upper Extremity Scale (FMA-UE) as the primary metric. Secondary outcomes include balance function, neuropsychiatric behavior, fall risk, daily living activities, and quality of life. This study aims to provide insights into the therapeutic benefits of DBS for post-stroke hemiplegia patients.

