## Methods and analysis

### Study design

The trial is a multicenter, prospective, double-blind crossover randomized controlled trial (RCT). The overall process is in Figure 2. In this study, we will include 62 moderate to severe post-stroke hemiplegia patients who had stable disease after 1 year of conservative treatment in multiple neuro medical centers in the General Hospital of the People’s Liberation Army of China et al. All patients included in the study will undergo deep brain electrode implantation. They will be randomly postoperatively divided into a DBS group and a control group, with 31 patients in each group. 1 month after surgery, the DBS group will be given electrical stimulation treatment, while the control group will undergo routine observation. Following up in the 3rd and 6th months after surgery. After the follow-up, all patients will stop electrical stimulation treatment for 2 weeks. After the 2-week washout period, the control group will start electrical stimulation treatment, and the DBS group will continue observation. Outpatient follow-up in the 6th and 9th months after surgery. After the follow-up, all patients will undergo electrical stimulation treatment. Observe for a long time. The leading outcome measure of follow-up is the pre-and post-change score on the Fugl-Meyer Assessment Upper Extremity Scale (FMA-UE). In addition, we will follow up on changes in the secondary outcomes of balance function, neuropsychiatric behavior, Post-stroke Spasticity, fall risk, activities of daily living, and quality of life.

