### Methods

#### Sample size

This study is a randomized, double-blind, active sham stimulation control design, and statistical experts determined that the sample ratio between the DBS group and the control group was 1:1. A review of the literature revealed that subjects’ upper limb FMA scores improved by an average of 7 points. Since this study was based on the changes in the mean FMA before and after DBS treatment, based on literature data, the mean FMA before DBS treatment was 21.92 ± 6.30, and the mean FMA after DBS treatment was 35.42 ± 12.23. This study is designed as a difference test to determine whether the mean of the DBS group (u1) is different from the mean of the control group (u2) (41, 42). The assumptions are as follows: H0: u1 − u2 = 0, H1: u1 − u2 ≠ 0. The two-sided significance level was 5%, the statistical power was 90%, and the dropout rate was 20% (43). The total sample size required for this study was calculated by PASS V.15 sample size calculation software to be 48 patients, with 24 people in each group. According to the possibility of electrode implantation deviation and other special circumstances leading to a lose, we included 62 patients, 31 in each group.

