#### Randomization

The 62 patients will be enrolled in the group undergoing deep brain electrode implantation. The 62 patients will be randomly divided into two groups at a ratio of 1:1 using a simple random grouping method, with 31 patients in the DBS group and the control group. First, random numbers will be automatically generated by the OpenClinica clinical trial data management platform to achieve centralized randomization. When a new patient meets the inclusion and exclusion criteria and signs the informed consent form, each research center can apply for the patient’s randomization number after filling in the patient’s basic information in OpenClinica. The random numbers will be automatically issued by the system, and only one coordinator in each center has access. All patients included in the study will receive DBS implantation after baseline assessment and were then randomly divided into two groups in a 1:1 ratio: DBS treatment group and control group. The former will start electrical stimulation treatment 1 month after the operation. Specialists will assess the patient’s recovery status through the remote rehabilitation system every week and guide rehabilitation training and electrical stimulation treatment. The latter will receive the same rehabilitation training under the face-to-face guidance of experts, except for the power-on (sham stimulation, the power-on stimulation parameter was 0). Experts will evaluate the patient’s recovery and adjust rehabilitation strategies every week in the outpatient clinic. The study is blinded to participants, scale raters, and data analysts. Allocation information will be kept in opaque, sealed envelopes by a designated person not involved in the study, thus ensuring the concealment of random assignment.

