
### Data analysis

All data analysis will based on IBM SPSS Statistics 25.0, describing the total score of each scale at each follow-up and the change from baseline at each visit after treatment. Measurement data using mean ± standard deviation to describe. Count data Use numerical values (%) to describe, and use group t-test or Wilcoxon to compare between groups according to the characteristics of the data. Intra-group comparisons were performed using rank sum-test, paired t-test or paired signed rank-test. For comparisons of pre-and post-treatment change values based on baseline general information, appropriate multivariate analysis models were used to correct for the effects of confounding factors or covariates based on the data situation. The single-item count data of each scale used the chi-square test or the exact probability test, and the grade data used the Wilcoxon rank sum test. A paired rank sum test and repeated measures analysis of variance were used to analyze the changes in score data within the group before and after treatment. The effectiveness measurement index is the improvement rate of each clinical scale at different follow-up times = (scale score at each postoperative time point − preoperative score) / preoperative score * 100%. A score improvement rate > 25% is considered effective. Safety observation indicators are all postoperative adverse reactions, including surgery-related adverse reactions, device-related adverse reactions, and stimulation-related adverse reactions. The type, number of cases, occurrence time, treatment measures, and prognosis of adverse events are recorded. The incidence of adverse events is defined as the number of patients in which it occurs divided by the number of all patients, and an adverse event rate of less than 5% is considered safe.

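### The stated adverse event incidence and its 5% safety verdict pool stimulated, sham, off and washout time, so the headline safety result does not use the randomised sham control

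*Protocol article*

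**What the plan says.** The article defines adverse event incidence twice, in the same terms. Under Adverse events: "The incidence of an adverse event was defined as the number of patients in whom it occurred divided by the number of all patients". Under Data analysis: "The incidence of adverse events is defined as the number of patients in which it occurs divided by the number of all patients". The second definition leads straight to the decision rule: "divided by the number of all patients, and an adverse event rate of less than 5% is considered safe". Neither place splits the rate by arm, period or stimulation state.

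The design supplies a concurrent control. On implantation, Study design states: "All patients included in the study will undergo deep brain electrode implantation". Randomization describes the control condition as "sham stimulation, the power-on stimulation parameter was 0". On the second period the abstract says: "Subsequently, the control group will receive electrical stimulation, while the DBS group will undergo sham stimulation". There is also an unstimulated first month after surgery, a two-week washout, and a later phase in which everyone is stimulated. Table 2 schedules adverse event recording from surgery to month 12.

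The article does provide for more than the bare incidence. Under Adverse events it asks for event counts and frequencies (all, related, serious, and leading to withdrawal), for the time of each event on the case report form, and for an assessment of its relation to the intervention. Under Data analysis it sorts the safety indicators into classes, "including surgery-related adverse reactions, device-related adverse reactions, and stimulation-related adverse reactions".

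**The concern.** Safety is one half of the leading purpose given in the Introduction, and the article presents the trial as the first of this target in stroke survivors. The events it expects also occur in these patients without stimulation: it calls falls common after stroke and puts post-stroke depression at 40% to 50%. For such events a randomised comparison of stimulation with sham is the main protection against misattribution.

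The stated rate does not make that comparison. An event during sham adds to the numerator exactly as one during stimulation does. The general between-group comparison under Data analysis is not tied to adverse events. If it were applied to a whole-study incidence, it would compare two treatment orders that both contain stimulation and sham, so much of any stimulation effect would cancel.

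Attribution by judgement is what remains. The Blind method section says the operating doctor cannot be blinded, and the Discussion accepts that active stimulation is likely to be noticed.

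**Working it through.** The 5% limit is given without derivation, so there is no figure of the plan's own to reproduce. The check asks what the pooled rate can and cannot show.

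**Inputs.** From the article: "we included 62 patients, 31 in each group"; one stimulation and one sham period per patient; denominator all patients; limit below 5%. Assumed, because the article gives no event rates: 5% to 10% per period on sham and 5% to 25% on stimulation. Events in the two periods are taken as independent.

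**Formula.** Pooled incidence over the two blinded periods = 1 − (1 − p_sham)(1 − p_on).

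| Assumed sham | Assumed on | Pooled | Pooled, of 62 | By state, of 62 (sham v on) |
|---|---|---|---|---|
| 10% | 10% | 1 − 0.90 × 0.90 = 19.0% | about 12 | about 6 v 6 |
| 5% | 15% | 1 − 0.95 × 0.85 = 19.25% | about 12 | about 3 v 9 |
| 5% | 5% | 1 − 0.95 × 0.95 = 9.75% | about 6 | about 3 v 3 |

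The first two rows describe no harm and threefold harm, yet both would be reported as about 12 of 62. The by-state columns separate them. The third row has no stimulation effect and still fails the rule.

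**Dependence between periods.** Whatever the dependence, the pooled rate lies between the larger of the two rates and their sum. For 5% and 5% that is 5% to 10%, so the rule is not met anywhere in the range. For 10% and 10% it is 10% to 20%, and for 5% and 15% it is 15% to 20%. The near-identity of 19.0% and 19.25% depends on independence, but the ranges overlap, so a pooled figure alone does not identify the contrast. Adding the off month, washout and open-label time can only raise these figures.

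**What meeting the rule would show.** The rule allows at most 3 of 62, since 3/62 = 4.84% and 4/62 = 6.45%. The exact two-sided 95% upper limit for 3/62 is 13.5%. If the true pooled rate is 5%, the rule is met with probability 62%; if it is 10%, with probability 12%.

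**What a by-state comparison could deliver.** For 5% on sham against 15% on stimulation, power is about 26% in period 1 alone (31 v 31, two-sided 5%) and about 34% with a within-patient exact McNemar test over both periods (62 patients, simulated). For 5% against 25% the McNemar figure is about 86%. The comparison is therefore mainly a difference with an interval.

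**The case against.** The strongest reply is that the quoted sentence is an ordinary per-patient incidence, that an overall incidence does not exclude tables by period, and that such tables are commonly left to an analysis plan, which is not shown here. This stands as far as absent tables go, and no fault is found on that ground. It does not cover the stated decision rule: the article itself attaches its safety verdict to the pooled rate.

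A reader might go further in four ways that the documents do not support.

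- *Stimulation harm is impossible to separate from background events.* Event times, an assessment of relation to the intervention and a stimulation-related class are all recorded, so a table by state could be built from the planned data. The depression scale and the fall-risk scale are also scored at each postoperative visit in both groups.
- *Events are counted only once per patient.* That is true of the incidence, but the same section also asks for the number and frequency of events.
- *Within-patient on versus sham is the only unbiased evidence.* That contrast is open to carry-over after a two-week washout, and grouping only by actual device state is an as-treated analysis. The article allows parameters to be adjusted for discomfort, so state may follow from earlier events. The randomised first period avoids carry-over.
- *The all-patient denominator halves the stimulation-related rate.* Controls are stimulated after the crossover and their events enter the numerator, so halving would require no such events among the second 31.

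It is also fair to say that the article does not state who judges relatedness. Unblinded attribution is a possibility, not an established fact.

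**Conclusion.** The point holds in a limited form. The incidence is defined twice over all patients, and the below-5% verdict is built on it. Both pool stimulated, sham, off and washout time, so the headline safety result does not use the randomised sham control and stimulation harm is left to case-by-case attribution. No harm and a threefold excess can give nearly the same reported rate (19.0% and 19.25%), and a harmless 5% per period gives 9.75% and fails the rule. These figures rest on assumed event rates and independent periods. They illustrate the problem and do not estimate its size in this trial. Nothing here says that the needed data are not collected. The change is worth making because it costs little and alters what the trial can conclude about stimulation safety, although the added comparison will be imprecise with 62 patients.

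**What to change.** Keep the overall incidence and event counts over all implanted patients; they suit surgery- and device-related events. Then add to the Data analysis section:

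1. Incidence, and events per patient-month, by period and stimulation state at onset: surgery to activation, on, sham, washout, open-label on. The denominator is the patients who entered that state.
2. The on-minus-sham difference with its 95% confidence interval, by assigned treatment: first for randomised period 1, which is free of carry-over, then within patients over both blinded periods. Label it descriptive, because power is low.
3. A statement that the pooled rate set against 5% is not the verdict on stimulation safety.

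The abstract and Study design place the second-period visits at different months, so the schedule must be reconciled before periods can be assigned.

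The cost is a change of analysis wording and one derived variable. Onset time is already on the case report form, and no further data, visits or patients are required.
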